## Early stopping rules

Every hundred patients included, the three treatment groups will be compared regarding :

- the lethality,
- the proportion of therapeutic failures at the end of hospitalisation, defined by the presence of trypanosomes in the CSF and/or the blood,
- the frequency of occurrence of serious adverse reactions

If the proportion of one of these events is significantly higher in one treatment group as compared to the other groups, the recruitment in this group will be stopped.

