## Results and side effects of treatment with melarsoprol

In the late-stage disease, the cure rate after treatment with melarsoprol is estimated to be greater than 95% (10,11,14). The principal risk is that of reactive encephalopathy (5.9% of cases treated with melarsoprol in a series of 1083 patients in Zaire (15), with a high mortality rate (67.2% in the same series). In an Ivory Coast series with 350 patients (6), arsenical treatment was associated with minor side effects, such as isolated febrile episodes, pruriginous rashes and subcutaneous cellulitis, sometimes followed by necrosis at the injection site, in 11.4, 4.6 and 2.8% of cases, respectively.

MSF data from Adjumani in Northern Uganda provide the following figures: among 3110 late-stage patients treated with melarsoprol, 567 (18.2%) patients suffered side effects, including 194 (6.2%) cases of reactive encephalopathy. The lethality observed during treatment was 5.5% (170/3110). The lethality of reactive encephalopathies was 51.5% (100/194). The median duration of hospitalisation was 25 days (unpublished MSF data).

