**1.4. Drug combinations**

The combination eflornithine + melarsoprol has proved synergistic in a murine model (22) and effective in one human case after 3 ineffective courses of treatment with melarsoprol alone and 1 ineffective course of treatment with eflornithine per os alone (23). There is a rationale for introducing melarsoprol at the end of treatment with eflornithine, as melarsoprol is more active when the trypanothion pool has been reduced by eflornithine (22).

Nitrate derivatives might potentiate the effects of arsenicals at the level of trypanothion.

In RDC, 69 patients have been treated with the combination nifurtimox + melarsoprol. One of them is dead, and no relapse was recorded after 12 months of follow-up ([name], personal communication)

We have no knowledge either of series of cases treated with a combination of nifurtimox + eflornithine. However, the combination of eflornithine with a nitrate derivative (free radical generator) such as nifurtimox should be beneficial in terms of the toxicity of the nitrate derivatives (reduction in dosage as a result of a synergism of action).

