## Alternative hypothesis

The difference in the cure rates between 2 groups obtained during the treatment of patients in the meningo-encephalitic phase is less than or equal to 10%.

If the observed difference in cure rates between the 2 groups is less than 10%, the null hypothesis will be rejected and the two treatments will be considered equivalent. The risk of error will then be 5% (alpha error) because if the difference in actual cure rates between the 2 treatments is greater than 10%, there is a 95% chance of demonstrating it (alpha error). Conversely, if the observed difference in the observed cure rates between the two groups is greater than 10%, the null hypothesis will not be rejected and the 2 treatments will be considered different, at a beta error set at 20%. The allocation ratio will be uniform (1 patient in group A to 1 patient in group B to 1 patient in group C).

Assuming a 95% cure rate, a maximum difference in cure rates between the groups of 10%, an identical drop-out rate in the 3 groups, an alpha error of 5% (one-sided test) and a power of 80%, this yields a sample size of 130 patients to be included in each group, i.e. 390 patients in the study. Allowing for a 10% drop-out rate, a final figure of 145 patients per group is obtained, i.e. 435 patients in total.

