**3.4. Study duration**

If a treatment centre treats about 500 late-stage patients annually, allowing for the inclusion criteria, which restrict the potential recruitment, it may be estimated that patient recruitment to the study will be completed within a maximum of 12 months. As the patients are followed up subsequently for 24 months, the total study duration is estimated at 36 months.

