**3.5. Randomisation**

Patients will be randomised on D1 (inclusion date), the day on which treatment is initiated. A fixed randomisation method will be used: the probability of being assigned one or other treatment will remain constant throughout the study.

The patients’ demographic, laboratory or clinical features might change during the study because of the control programme in progress. A blocking process in the randomisation will ensure that a comparable number of patients is included in each group at all times. The blocking procedure will not be disclosed to the field team before the end of the enrolment period.

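### The only rule that can close an arm first acts at 100 inclusions, about 33 patients per arm, so two little-documented combinations start with no written trigger to pause recruitment

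*Protocol*

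**What the plan says.** Section 3.6, Early stopping rules: "Every hundred patients included, the three treatment groups will be compared regarding" three events, namely lethality, parasitological failure at the end of hospitalisation, and serious adverse reactions. Recruitment to a group stops if one of these is significantly more frequent there than in the other groups.

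Section 3.3 gives "a final figure of 145 patients per group is obtained, i.e. 435 patients in total" with 1:1:1 allocation. Section 3.4 expects that "patient recruitment to the study will be completed within a maximum of 12 months". Section 3.5 uses blocks to keep the groups comparable in number at all times.

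On earlier human experience, section 1.4 describes B as "effective in one human case after 3 ineffective courses of treatment with melarsoprol alone" (and one of oral eflornithine). For C it says "We have no knowledge either of series of cases treated with a combination of nifurtimox + eflornithine". For A (melarsoprol + nifurtimox) it reports that "69 patients have been treated with the combination nifurtimox + melarsoprol", with one death.

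Other safety provisions act on individuals or on procedures. Under Side effects, the clinician may withhold or resume one patient's treatment. The withdrawal paragraph concerns single patients. Section 5.2 has a field doctor and the principal investigator supervise procedures, after a one-month field test.

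**The concern.** The first patients on B and C receive combinations for which the protocol documents almost no human experience. If one combination is unexpectedly lethal, the clinician can stop treating the patient in the bed, but nothing written says when the next patient should no longer be randomised to that arm. That decision is first scheduled after about 33 patients per arm. At stake are the patients enrolled in a harmful arm between the point where its deaths are already striking and the hundredth inclusion.

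The interval is set by the protocol itself. It is not a detail left to a statistical analysis plan. The test and significance level behind the comparison may be in such a plan and are not criticised here.

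**Working it through.** **Timing of the first look.** Per arm: 100/3 = 33.3 patients. Pace: 435/12 = 36.25 per month if even (assumption), so 100/36.25 = 2.8 months. Expected deaths in 33 patients: 33 × 0.055 = 1.8 at the melarsoprol lethality of 5.5% (170/3110, section 1.1), and 33 × 0.20 = 6.6 at an assumed 20%.

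**What the first look can detect on deaths alone.** The test is not stated. Assume a two-sided 5% Fisher test of one arm (33) against the other two pooled (66), computed exactly:

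| True lethality of the arm | 10% | 15% | 20% | 30% |
|---|---|---|---|---|
| Both other arms at 5.5% | 11% | 30% | 53% | 88% |
| One at 1/69, one at 5.5% | 24% | 49% | 71% | 95% |

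Over repeated looks (6,000 simulated trials), a 20% arm is flagged by the second look in 86% of trials in the first setting and 96% in the second.

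**What the first look can detect on serious adverse reactions.** Section 1.1 gives 6.2% encephalopathy with 51.5% lethality. Suppose all excess deaths in a melarsoprol arm come through encephalopathy. Then 15% lethality implies 6.2% + (15% − 5.5%)/0.515 = 24.6% encephalopathy, and 20% implies 6.2% + (20% − 5.5%)/0.515 = 34.4%. The same Fisher test with the other arms at 6.2% flags about 68% and 93%. This does not apply to C, which contains no melarsoprol.

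**A running death count, A and B.** Reference 5.5%. Pause at 3 deaths within 8 patients, 4 within 15, 5 within 24 or 6 within 33. With f(n, d) the probability of having reached patient n with d deaths and no pause, f(n, d) = (1 − p)·f(n−1, d) + p·f(n−1, d−1), removing at each n the states at or above the boundary. The removed probability sums to the chance of a pause.

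| True lethality | 5.5% | 8% | 15% | 20% | 30% |
|---|---|---|---|---|---|
| Paused by patient 33 | 2.1% | 7.5% | 44% | 72% | 97% |
| Mean patients at pause, paused arms only | – | – | 18.1 | 16.7 | 12.2 |
| Mean patients saved over all arms, after lag | – | – | 4.6 | 8.4 | 15.4 |

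The lag allows for patients already enrolled while outcomes mature over the 12-day stay: 36.25/3 = 12.1 per arm per month × 12/30 = 4.8, taken as 5. The saving sums P(pause at n) × max(0, 33 − n − 5); arms never paused contribute zero.

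**A running death count, C.** Reference assumed at 2%. Pause at 2 within 8, 3 within 24 or 4 within 33. It pauses 2.0% of arms at a true 2%, 5% at 3% and 19% at 5.5%. It pauses 53%, 81% and 94% of arms at 10%, 15% and 20%, at a mean of 15.5, 13.7 and 11.4 patients among those paused.

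**Unnecessary pauses across the three arms.**
- References hold: 1 − (1 − 0.021)² × (1 − 0.020) ≈ 6%.
- A and B truly at 8%: 1 − (1 − 0.075)² × (1 − 0.020) ≈ 16%.
- C truly at 5.5% against the 2% boundary: 1 − (1 − 0.021)² × (1 − 0.19) ≈ 22%.

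**The case against.** The strongest reply is that this asks for an additional rule and does not show an error. The stopping rule names its events, its interval and its action, and nothing in the protocol contradicts a look every hundred patients. That is fair, and it is why the point is an improvement to consider. It does not remove the gap: the interval is fixed in the text, and the document shown has no earlier arm-level trigger.

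Secondly, the early patients are not unprotected. They are inpatients throughout treatment in an open trial, so deaths are visible by arm at once. Eflornithine and nifurtimox are given at doses already used in the programme. Nifurtimox runs for 10 days against the more usual two weeks, and melarsoprol is at 1.8 mg/kg/day against 2.16 in the 10-day schedule under evaluation elsewhere. The first 50 subjects have blood counts at D1 and D12. All this stands as mitigation. None of it states when an arm should be paused, and programme doses of the single drugs say little about the combinations.

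Thirdly, a reader might infer from the deaths-only figures that the count detects more than the planned comparison. The documents do not support that in general. If excess deaths in a melarsoprol arm arise through encephalopathy, the planned comparison of serious adverse reactions flags about 68% and 93% of arms at 15% and 20% lethality, against 44% and 72% for the count. The count's advantage is then timing only.

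Finally, for B the gain is small at moderate harm: 4.6 × (0.15 − 0.055) ≈ 0.4 deaths at 15%, and 8.4 × (0.20 − 0.055) ≈ 1.2 at 20%. For C it rests on a reference rate that the documents do not supply. Both remarks stand.

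**Conclusion.** The point holds as one of timing. No written rule can pause an arm before about 33 patients have entered it, and for B and C the protocol documents almost no earlier experience. A reader might go further and infer that a dangerous arm would escape detection, or that safety is unsupervised. Neither follows. On deaths alone a 20% arm is flagged by the second look in 86% to 96% of trials, and clinicians and supervisors are in place from the first patient.

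The benefit of an earlier trigger is modest at 15% lethality against 5.5%, where the A/B boundary still misses 56% of arms by patient 33. It is clearer at 20% to 30%, and for C if its reference rate is set low. These sizes assume even accrual, independent deaths, a Fisher test that the protocol does not specify, and, for C, an assumed 2%. This is a low-cost improvement worth considering; it does not undermine the trial's design.

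**What to change.** Keep the hundred-patient comparisons. Add one paragraph to Early stopping rules: from the first patient, the field doctor and the principal investigator keep a running count of in-hospital deaths per arm, and recruitment to an arm is paused for review, not stopped, when a boundary is crossed.

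- A and B, against 5.5%: 3 deaths within 8 patients, 4 within 15, 5 within 24, 6 within 33.
- C, against a lower rate that the sponsor fixes and justifies in advance. Example at an assumed 2%: 2 within 8, 3 within 24, 4 within 33.

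After 33 patients per arm the existing comparisons take over.

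This needs no new committee and no new data. The price is about a 6% chance of at least one unnecessary pause if the reference rates hold, and about 16% to 22% in the less favourable cases above. A fixed historical reference can also be tripped by a change in case mix. Section 3.5 itself warns that patients' "demographic, laboratory or clinical features might change during the study because of the control programme in progress", which a concurrent comparison resists better. That is why crossing the boundary should lead to a review and not to closure.

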**1. Context**

**1.1. Current protocols for the treatment of HAT - Toxicity of melarsoprol.**

## Standard protocols

The treatment of HAT depends on the stage at which the disease is diagnosed.

· Pentamidine in the hemo lymphatic phase

Pentamidine isethionate, an aromatic diamine, is the reference drug used for the treatment of early-stage HAT. Patients are hospitalised and receive 4 mg/kg of pentamidine in a daily intramuscular injection for 7 to 10 days.

· Melarsoprol in the meningo-encephalitic phase

The treatment of patients with late-stage disease involves the use of melarsoprol, a trivalent arsenical derivative requiring a more intense protocol and hospitalisation for 25 days. Melarsoprol has been used almost exclusively in the treatment of late-stage HAT for more than 40 years (10). The mode of action of melarsoprol is poorly understood. According to one generally accepted theory (although recently disputed), melarsoprol acts by depriving the trypanosome of trypanothion by binding irreversibly to it. Trypanothion, which is the analogue of glutathion in trypanosomes, protects the parasite from free radicals. The pharmacokinetic of melarsoprol is poorly understood, but it appears that the half-life of the drug is 35 hours. Melarsoprol crosses the blood-brain barrier in limited quantities (10,11).

In a common protocol with Melarsoprol, patients receive three series of three intravenous injections separated by rest periods of six days. The doses of melarsoprol are progressive, from 1.8 to 3.6 mg/kg/day. Prednisolone is combined systematically, as a preventive measure against reactive encephalopathy (12).

A continuous treatment schedule (2.16 mg/kg/day for 10 days) simplifying the protocol and reducing the hospitalisation period is currently under evaluation in several countries. Preliminary results show equivalent efficacy and similar safety to the standard therapeutic regimen (13).

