**1.2. Increase in therapeutic failures with melarsoprol**

In Arua in north-west Uganda, about 25% of cases of HAT treated for the first time with a complete course of melarsoprol result in therapeutic failures (the usual therapeutic failure rate after treatment with melarsoprol is less than 5% (10,14). In addition, repeated courses of melarsoprol in cases that had relapsed initially do not produce a cure in these patients (9,16). An identical phenomenon has appeared in Southern Sudan, in the region of Ibba, where a 6-month relapse rate of 30% has been observed (unpublished MSF data). High relapse rates after treatment with melarsoprol have already been reported in the past, particularly in Zaire (10).

Supplementary analyses on strains circulating in the Arua region have shown that the high therapeutic failure rate observed in this region was due to the appearance of melarsoprol-resistant strains of trypanosomes (17).

This phenomenon, which may extend to other sites, constitutes a major public health problem because of the lack of second-line drugs for the treatment of late-stage HAT.

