**1.3. Other drugs used for the treatment of late-stage HAT**

## Eflornithine

Difluoromethylornithine (eflornithine or DFMO) has been the only new molecule introduced in the treatment of HAT over the last few decades. Eflornithine was used successfully in the treatment of late-stage HAT during the 1980s (4,10). It is a trypanostatic drug, which acts as an inhibitor of ornithine decarboxylase (an enzyme acting on the cycle of synthesis of polyamines, which themselves are involved in cell multiplication and differentiation) (10,11). This ornithine decarboxylase inhibition activity also causes a reduction in the synthesis of trypanothion, which would allow a synergistic action between eflornithine and melarsoprol. The half-life of eflornithine is short (3.3 hours) (10,11). Eflornithine readily penetrates the cerebrospinal fluid (CSF) and its concentration in the CSF is higher in adults and patients already treated with melarsoprol, probably because of the greater permeability of the blood-brain barrier (18). This might explain why a lower therapeutic failure rate is observed in patients treated with eflornithine after melarsoprol failure, but with a higher frequency of side effects (unpublished MSF data).

Eflornithine is better tolerated than melarsoprol, even if its prescription causes the occurrence of a number of side effects, all reversible and without consequences on discontinuation of treatment: pancytopenia, diarrhoea (particularly when eflornithine was taken orally), convulsions, hallucinations, insomnia, hearing loss, alopecia. In patients treated with eflornithine after melarsoprol failure, a continuous course of treatment for 7 days (100 mg/kg every 6 hours) appears to have the same efficacy as a 14-day treatment (19).

The availability of eflornithine has become erratic, the manufacturer having discontinued the production process after the recent manufacture of a final batch of product ensuring the short-term availability of the drug. However, the medium-term availability of eflornithine depends on the identification of a new laboratory prepared to take on the production.

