**3.7. Follow-up of patients**

**Table 2 : Timetable of activities during the study**

| **ACTIVITIES** | **D1** | **D2-11** | **D12** | **M6** | **M12** | **M24** | **Non-scheduled days** |
| --- | --- | --- | --- | --- | --- | --- | --- |
| **Informed consent– Inclusion** | X |  |  |  |  |  |  |
| **Randomisation** | X |  |  |  |  |  |  |
| **Clinical evaluation** | X | X | X | +/- | +/- | +/- | +/- |
| **Parasitological evaluation**  Woo  QBC  GP  LP | X  X  +/-  X |  | X  +/-  X | X  +/-  X | X  +/-  X | X  +/-  X | X  +/-  X |
| **Biological evaluation**  CSF white cells counts  Haematocrit Y  WBC count Y  Differential count Y | X  X  X  X |  | X  X  X  X | X | X | X | X |
| **Sampling for Antwerp study**  CSF sample collection  Serum sample collection | X  X |  | X  X | X  X | X  X | X  X | X  X |
| **Treatment**  Prednisolone *  A : Melarsoprol+nifurtimox  B : Melarsoprol+eflornithine  C : eflornithine +nifurtimox | X | X  X  X  X |  |  |  |  |  |
| **New therapeutic scheme if treatment failure** |  |  | X | X | X | X | X |

Y Only for the first 50 subjects

* Only for treatments A or B

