## Follow-up duration

Patients included in the study will be monitored for 24 months after the end of treatment.

Laboratory tests (lumbar puncture, glandular puncture, QBC, haematology) and clinical examinations will be undertaken at the end of hospitalisation and 6, 12 and 24 months after the end of the treatment.

A network of community health workers will ensure the presence of the patients included in the study at the 3 scheduled follow-up visits as far as possible. In addition, the address of each patient included in the study will be noted at the time of admission. Anyone missing a follow-up visit will be sent a reminder 3 times.

Apart from this, the patient will be allowed to come at any time in the trypanosomiasis treatment centre throughout the follow-up period.

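### The efficacy part of the early stopping rule looks only at the end of hospitalisation and leaves out the month-6 failures that the trial already records

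*Protocol*

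**What the plan says.** The Early stopping rules (section 3.6) open with "Every hundred patients included, the three treatment groups will be compared regarding" and list three items: lethality, "the proportion of therapeutic failures at the end of hospitalisation, defined by the presence of trypanosomes in the CSF and/or the blood", and serious adverse reactions. If one of these is significantly more frequent in one arm, "the recruitment in this group will be stopped". No significance level is given.

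Section 3.7 fixes when efficacy is observed. Tests "will be undertaken at the end of hospitalisation and 6, 12 and 24 months after the end of the treatment", and the timetable of activities has one post-treatment column, D12, before month 6. The classification of responses lets a patient be declared a failure at any control visit, on parasites or on a CSF cell count of at least 20 that has risen since the end of treatment. Month-6 failures are therefore identified and acted on for the individual patient, but they do not enter the comparison between arms.

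Section 1.2 describes the failure problem behind the trial: about 25% failures after melarsoprol in Arua, and for Ibba "a 6-month relapse rate of 30% has been observed".

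**The concern.** Relapse happens after treatment ends, so a parasite examination at D12 cannot register it. It can only show infection that treatment did not clear. If an arm fails mainly by relapse, the efficacy criterion may give little or no signal. Randomisation to that arm could then continue while month-6 failures from it are already on file and those patients are being retreated. What is at stake is the number of patients still allocated to a poor arm late in accrual, and whether the only efficacy item in the rule can inform that decision.

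**Working it through.** The rule states no significance level, boundary or power, so it has no figure of its own to reproduce. What follows is an illustration.

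**Inputs from the protocol.** 435 patients, 1:1:1 (section 3.3); recruitment within at most 12 months (section 3.4); looks at 100, 200, 300 and 400 inclusions; a 10-day course followed by D12 and then month 6 after treatment; 25% and 30% failure (section 1.2); 5% failure, from the assumed 95% cure rate.

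**Assumptions.** Even accrual, every month-6 visit attended, two-sided 5% Fisher exact test, and 25-30% failure reached by month 6. The protocol gives no time point for the 25%.

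**Month-6 results available.** With rate r = 435/12 = 36.25 per month, a patient needs about 6 + 12/30.4 = 6.395 months from inclusion. The number available at look L is max(0, L - 6.395r). Since 6.395 × 36.25 = 231.8, looks 1 to 4 have 0, 0, 68 and 168 patients, or about 0, 0, 23 and 56 per arm.

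| Accrual | Look 1 | Look 2 | Look 3 | Look 4 |
|---|---|---|---|---|
| 9 months | 0 | 0 | 0 | 91 |
| 10 months | 0 | 0 | 22 | 122 |
| 12 months | 0 | 0 | 68 | 168 |
| 24 months (assumed) | 0 | 84 | 184 | 284 |

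**Power using month-6 failures (12-month accrual, exact enumeration).** Each range runs from 25% to 30% failure in the poor arm. At look 3 it also covers 22 or 23 patients per arm where the result depends on that split.

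| Comparison | Look 3 | Look 4 |
|---|---|---|
| One poor arm v the other two pooled | 0.62-0.77 | 0.94-0.99 |
| One poor arm v one other arm | 0.35-0.53 | 0.81-0.93 |
| Both melarsoprol arms poor: one of them v the other two pooled | about 0.12-0.18 | 0.31-0.41 |

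**Patients still to be enrolled.** After look 3: (435 - 300)/3 = 45 per arm. After look 4: (435 - 400)/3, about 12 per arm.

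**What D12 parasitology can show.** Let f be the share of eventual failures that are parasite-positive at D12; the protocol does not give it. With 25% v 5% failure, the D12 rates compared are 0.25f and 0.05f, with 33, 67, 100 and 133 patients per arm.

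| f | Arm v arm, looks 1-4 | Arm v other two pooled, looks 1-4 |
|---|---|---|
| 0 | 0 / 0 / 0 / 0 | 0 / 0 / 0 / 0 |
| 10% | 0 / 0.005 / 0.025 / 0.067 | 0.04 / 0.15 / 0.28 / 0.39 |
| 20% | 0.004 / 0.067 / 0.194 / 0.331 | 0.15 / 0.39 / 0.54 / 0.65 |

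**False stopping from the added comparison.** With 5% failure in every arm, the chance that a given arm is found significantly worse than the other two pooled is about 1.6-2.3% per look.

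**The case against.** The rule says openly what it measures and nowhere claims to detect relapse. It follows the paragraphs on side effects and withdrawal, and two of its three items concern safety, so it can fairly be read as acute monitoring, with relapse left to the 24-month outcome. That stands: there is no contradiction here.

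It also stands that the benefit comes late and depends on the scenario. The highest power arrives when few patients remain to be enrolled. Twelve months is the protocol's stated maximum, and faster accrual leaves little or nothing at the third look. The resistance that section 1.2 describes is to melarsoprol, which is in two arms, and then power is low. The 25% and 30% come from melarsoprol treatment, not from these combinations. Section 1.4 mentions 69 patients given nifurtimox with melarsoprol and no relapse recorded after 12 months.

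Three stronger readings are tempting and are not supported:
- **Residual drug.** Section 1.1 says of melarsoprol that "it appears that the half-life of the drug is 35 hours", so a reader might infer that drug still present at D12 is what hides failure. Arm C contains no melarsoprol and is just as blind to relapse at D12, so this is not the reason.
- **Cell count.** A reader might infer that CSF cell count was wrongly left out. Before month 24 the classification requires a rise since the end of treatment, or two consecutive rises. The D12 count is itself the end-of-treatment value, so neither condition can be met then.
- **Certain silence.** A reader might infer that the D12 criterion must stay silent. That depends on how many failures are already parasite-positive at D12, which the protocol does not say. If it were 20%, power against the pooled arms would be 0.54-0.65 at the last two looks.

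**Conclusion.** The point holds as a cheap improvement. As fixed, the efficacy criterion can reveal persistent infection only, although the protocol expects failure to appear over months and classifies it at month 6. Under even 12-month accrual and full attendance, adding month-6 failures would give a moderate to good chance of identifying a single poor arm at the third look (0.62-0.77 pooled, 0.35-0.53 arm against arm), with about 45 patients per arm still to come. By the fourth look detection is likely, but only about 12 per arm remain. The addition does nothing at the first two looks under that accrual, and it is weak if both melarsoprol arms fail. Slower accrual would increase its value and faster accrual would reduce it. All power figures rest on an assumed two-sided 5% Fisher test, because the rule states no level. Lethality and serious adverse reactions are separate criteria and are unaffected.

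**What to change.** In the Early stopping rules, extend the efficacy comparison to include failures, as defined in the classification of responses, among patients who have reached month 6. Tabulate them by arm, with the number who have reached that visit, at every look where such data exist. Keep the end-of-hospitalisation parasite result alongside. State the significance level of the rule and count the added comparison when setting it.

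The cost is protocol wording plus one further table at the later looks; no new visit or test is needed. The downside is one more repeated comparison, with the false-stopping risk shown above, and no help at the early looks.

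### The early stopping rule closes an arm on an undefined significance finding over up to four looks and three events, so its false-closure risk is anywhere from about 2% to about 40% on a conventional two-sided 5% Fisher test

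*Protocol*

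**What the plan says.** Protocol section 3.6, Early stopping rules, sets the schedule: "Every hundred patients included, the three treatment groups will be compared regarding" three events. They are "the lethality", "the proportion of therapeutic failures at the end of hospitalisation, defined by the presence of trypanosomes in the CSF and/or the blood" and "the frequency of occurrence of serious adverse reactions". The trigger is a finding on any single event: "If the proportion of one of these events is significantly higher in one treatment group as compared to the other groups", then "the recruitment in this group will be stopped". The consequence is automatic.

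Section 3.3 sets the maximum size at 145 per group, "i.e. 435 patients in total". Its 5% one-sided error belongs to the final equivalence comparison. Section 3.8 compares the groups in pairs.

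Section 3.5 describes a fixed randomisation in which "the probability of being assigned one or other treatment will remain constant throughout the study". It also says that patient features may change during the study because of the control programme, and it uses blocking for that reason.

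**The concern.** One sentence decides whether a third of the design continues, and it can be applied in at least three ways: against the other two arms pooled, against either one, or against both. Each would be tested at a level the rule does not give, on three events, for three arms, at several looks. No overall error is stated.

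A chance closure cuts short two of the three pairwise comparisons. At the first look the closed arm would hold about 33 patients against the 145 planned. The event that triggered closure would also be overestimated in that arm, because it was selected for being high.

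Recruitment to the other arms would continue after closure. The pairwise analysis would then set an arm enrolled early against arms enrolled throughout, although section 3.5 itself expects the patient population to drift.

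**Working it through.** **The plan's own figures.** The protocol states no error rate for this rule, so there is none to reproduce. The size that drives the number of looks does reproduce: 130 / 0.90 = 144.4, rounded up to 145, and 3 × 145 = 435.

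**Number of comparisons.** 435 / 100 gives looks at 100, 200, 300 and 400. Then 4 looks × 3 events × 3 arms = up to 36 comparisons of an arm with the others. They are correlated across looks and events, so a formula for independent tests does not apply and the risk was simulated.

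**Inputs**
- Lethality 5.5% (170/3110), from the melarsoprol results in section 1.1.
- Serious reactions: no rate is given. Assumed 6.2% to 18.2%, anchored on encephalopathy (194/3110) and any side effect (567/3110) in the same series.
- Failure at the end of hospitalisation: no rate is given. Assumed 1–2%.
- Test and level: not given. Assumed Fisher's exact test, two-sided 5% per comparison.
- 1:1:1 allocation, deaths counted within serious reactions, outcomes known at each look.

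**Quantity computed.** The share of simulated trials with identical arms in which, at any look, any arm has a higher proportion with p ≤ 0.05 on any event.

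| Lethality / failure / serious reactions | v other two pooled | v either other arm | v both, separately | pooled, p<0.005 |
|---|---|---|---|---|
| 5.5 / 1 / 6.2% | 28% | 14–18% | about 2% | 2.5% |
| 5.5 / 1 / 10% | 33% | 22–25% | about 2–3% | 3.2% |
| 5.5 / 2 / 18.2% | 39% | 28–33% | about 3% | 3.9% |

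The ranges in the third column reflect whether the arms are exactly equal or 34/33/33 at the first look. Fisher's test is coarse at that size.

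**Sensitivity.** Over wider assumed rates (lethality 2–10%, failure up to 10%, serious reactions 6.2–20%):
- Pooled: 28–43% with two-sided Fisher, 35–54% with the uncorrected z test. One-sided 5% gives 33–54% and 58–77%.
- Both arms exceeded separately: 2–6% with two-sided Fisher, 6–10% with two-sided z. One-sided z reaches 18–27%.
- A global three-arm chi-square at 5%: 21–29%.

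**Timing.** For the pooled comparison in the middle row, cumulative false closure is 11%, 20%, 27% and 33% over the four looks.

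**How few events decide it.** At the first look (33 v 67 pooled), 3 deaths against 0 gives p = 0.034 and 4 against 1 gives p = 0.040. The expected number in the smaller group is 33 × 0.055 = 1.8.

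**Price of a stricter rule.** Take one arm with deaths 8% v 4% and serious reactions 16% v 8%. Closure by 400 patients is about 77% with pooled p<0.05, about 38% with pooled p<0.005, and about 35% with p<0.05 required against both other arms. By 200 patients, moving from pooled p<0.05 to pooled p<0.005 lowers it from about 45% to about 15%.

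**The case against.** The plural in the rule, together with the pairwise analysis in section 3.8, makes exceeding both other arms at least as natural a reading as pooling. On that reading the false-closure risk is already low. This stands, and it is why no single figure can be attached to the rule. A reader might infer that the trial has a one-in-three chance of losing an arm by accident. The document does not support that, because the figure needs pooling, a two-sided 5% level, Fisher's test and assumed event rates.

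A reader might also take 5% as the protocol's only error level and carry it into this rule. That is not so: sections 3.3 and 3.8 also work at 20%, and the 5% is one-sided and tied to the final equivalence test.

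A test and its boundary are often left to an analysis plan, which is not at hand. That is fair for the choice of test. It does not cover a protocol rule that fixes the looks, the triggers and an automatic consequence while leaving its comparator open.

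The combinations have almost no prior human experience, so accepting more false closures in order to detect harm sooner is a legitimate choice. This stands too, but the choice should be made knowingly.

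The harm is also uneven. At the fourth look about 133 of 145 per arm are enrolled, so closure then costs about 12 patients. The inflated estimate concerns the triggering early event and bears only partly on 24-month failure. Finally, the closure rule is better read as an exception that section 3.5 omits than as a contradiction of it.

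**Conclusion.** The concern holds in conditional form. The rule permits readings whose false-closure risk differs about tenfold with identical arms and two-sided 5% Fisher tests: about 28–40% pooled, about 15–30% against either arm, about 2–6% against both. Uncorrected or one-sided tests raise all of these. The figures rest on assumed failure and serious-reaction rates, on lethality from melarsoprol alone (arm C contains no melarsoprol), and on outcomes being available at each look.

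The defect is that the protocol fixes neither the comparison nor the overall error. It does not follow that closure by chance is likely on every reading, or that the final equivalence test is itself inflated. The lack of a concurrent-enrolment restriction is a separate, smaller gap that rests on the protocol's own expectation of drift.

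**What to change.** 1. State which comparison applies (pooled, either or both), including what it becomes once an arm has closed. Choose the per-look threshold to meet a stated overall false-closure risk across looks, events and arms, and report beside it the chance of closing a truly worse arm. Two illustrations only: pooled p<0.005 gives about 3%, and p<0.05 against both other arms gives about 2%. The cost is slower closure: in the example above, about 35–38% by 400 patients instead of about 77%. The sponsor may reasonably accept a higher false-closure risk for that reason.
2. State that comparisons involving a closed arm use only patients randomised while that arm was open. The cost is a small loss of precision.
3. Add the exception for a closed arm to the constant-allocation sentence in section 3.5. This is wording only.

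Keep any unscheduled clinical safety review separate from this rule, so that a stricter statistical threshold does not restrict it.
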